### 5.22. Analysis Set

Safety Set (SS): All subjects enrolled who received the trial medication and had at least one subsequent safety visit. The SS will be used for the analysis of safety data.

Full Analysis Set (FAS): All enrolled subjects who received at least one dose of trial medication and had at least one efficacy evaluation. The FAS will be used for the efficacy analysis.

Per Protocol Set (PPS): A subset of the subjects in the FAS who are compliant with major requirements of the clinical study protocol. The PPS will be used for the auxiliary analysis for the efficacy analysis.

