## 3.2 Study Endpoints

- Primary endpoint:

Safety endpoint: the safety and tolerance of UC-MSCs in patients with primary ITP. The safety and tolerance of UC-MSCs will be evaluated according to the incidence and severity of adverse events and serious adverse events (according to NCI CTCAE 5.0 standard).

- Secondary endpoints:

Effectiveness endpoints:

1. Platelet counts at each visit point to evaluate the response rate.
2. Percentage of subjects with platelet counts≥50×10^9^/L and ≥100×10^9^/L at least once respectively.
3. Percentage of subjects with platelet counts ≥ 30×10^9^/L and 2-fold increase from baseline at least once.
4. The time required from the first infusion to platelet counts first ≥ 50×10^9^/L.
5. Percentage of subjects receiving emergency treatment
6. Percentage of subjects with reduced concomitant medications.
7. The longest duration of the subject's platelet counts continuously ≥ 30×10^9^/L.
8. Changes in bleeding scores (WHO bleeding scores) throughout treatment.

Pharmacokinetic endpoint:

Pharmacokinetic characteristics of UC-MSCs in patients with primary ITP, especially the concentration changes of UC-MSCs in peripheral blood.

Immunogenicity endpoint:

Incidence of UC-MSCs antibodies.

Other study endpoints:

Changes in immune status in vivo after UC-MSCs infusion.

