### 5.23. Statistical Analysis Methods

- Basic statistical methods

All statistical analyses will be conducted using SPSS 26.0 and GraphPad Prism 9.0 software, statistical analysis will be primarily descriptive. Quantitative data will be presented as median (interquartile range), and qualitative data will be presented as n (%). The differences between groups of quantitative data will be performed using student's t tests or Wilcoxon non-parametric tests. Qualitative variables will be tested with chi-square tests or Fisher's exact tests. The methods of Kaplan-Meier will be used to estimate the time-to-event data. All tests will be calculated with a two-sided significance level of 0.05.

- Safety analysis

Summary tables for adverse events have to include all AEs that occurred in the whole period of study. The correlation between treatment and AEs will be determined by the principal investigator.

- Effectiveness analysis

Proportions with 95% confidence intervals will be calculated for the efficacy endpoint.

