# Management of Infusion Reactions

## 10.1 Delay/Pause/Stop Administration

If subjects experience any of the following adverse events, it is recommended to suspend or discontinue the administration of UC-MSCs to allow the subjects to recover from the toxicity, whether the adverse events are related to the administration or not.

- Criteria for discontinuation of administration are as follows:

1. If severe allergy occurs during the infusion process, such as anaphylactic shock, the administration should be stopped immediately and patients should be withdrawn from the trial;
2. If arterial or venous thrombosis occurs during the infusion process, such as deep vein thrombosis, myocardial infarction, etc., the investigator needs to judge the correlation with the infusion of UC-MSCs, and determines whether to continue the administration;

- Criteria for delay of administration are as follows:

1. Severe bleeding symptoms, such as gastrointestinal hemorrhage, and cerebral hemorrhage;
2. Febrile or infectious neutropenia;
3. Grade 3 or higher non-hematological toxicity, except in the following cases:

- Grade 3 nausea that can resolve with antiemetic treatment within 7 days
- Grade 3 vomiting that can resolve with antiemetic treatment within 7 days
- Grade 3 diarrhea that can resolve with antidiarrheal treatment within 7 days
- Grade 3 fatigue
- Grade 3 Weakness

If any of the above adverse effects occur, it is recommended to pause umbilical cord-derived MSC dosing until recovery to ≤ Grade 2 or baseline; Dosing should be restarted according to treatment schedule (Grade 2 laryngeal edema or Grade 2 bronchospasm requires full recovery).

In addition, if the platelet counts are ≥300×10^9^/L during the infusion, the drug administration can be suspended until the platelet counts are less than 300×10^9^/L, and then the administration can be resumed.

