## 13.3 Measures of Shedding Cases

The CRF of cases withdrawn for any reason should be kept, the last test results will be considered the final results and will be used for the FAS analysis of their efficacy and adverse reaction. Those who respond to the UC-MSCs before completing the full course of infusion will not be considered as shedding cases but as response ones.

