## 13.4 Conditions of Study Suspension

Suspension of the trial means that the clinical trial does not end as planned but stops during the trial. The main purpose of the trial suspension is to protect the rights and interests of the subjects, ensure the quality of the trial, and avoid unnecessary economic losses.

1. If a serious safety problem occurs during the trial, the trial should be suspended in time.
2. The effect of the drug is found too poor or even ineffective and has no clinical value during the trial, the trial should be suspended to avoid delaying the effective treatment of the subjects and at the same time to avoid unnecessary economic losses.
3. The protocol of clinical trial is found to have major mistakes and it is difficult to evaluate the effect of drugs, or a well-designed protocol has a significant deviation in the implementation, and it is difficult to evaluate the effect of drugs if continues.
4. The sponsors request the suspension (such as funding reasons, management reasons, etc.).
5. The administrative departments cancel the test, etc.

A final assessment of the subject should be made at this time and the suspension of study should be recorded on the appropriate page of the CRF. Subjects who withdraw from the trial due to adverse events should be followed up by the investigator.

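### The Safety Set requires a safety visit after dosing, so a subject who dies or is lost after the first infusion is excluded on the literal wording; sections 5.22, 5.23 and 13.3 need reconciling

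*Protocol*

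**What the plan says.** Section 3.2 sets the primary endpoint: "The safety and tolerance of UC-MSCs will be evaluated according to the incidence and severity of adverse events and serious adverse events". Section 5.22 defines the Safety Set (SS) as "All subjects enrolled who received the trial medication and had at least one subsequent safety visit", and adds: "The SS will be used for the analysis of safety data". The same section defines the Full Analysis Set (FAS) by two conditions, at least one dose and at least one efficacy evaluation, and reserves it for efficacy.

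Five other places bear on who is counted:

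- Section 5.23, under safety analysis: "Summary tables for adverse events have to include all AEs that occurred in the whole period of study".
- Section 10.1, on severe allergy during an infusion: "the administration should be stopped immediately and patients should be withdrawn from the trial". Section 13.1 also lists death among the reasons for withdrawal.
- Section 13.3, on the last results of withdrawn cases: they "will be used for the FAS analysis of their efficacy and adverse reaction".
- Section 13.4: "Subjects who withdraw from the trial due to adverse events should be followed up by the investigator". Section 15.2 (item 5) adds that this follow-up lasts until the event has fully resolved.
- Section 8 (item 10) plans 3-5 years of follow-up for late adverse events in everyone infused, and 11.4 plans more than 2 years for malignancy. Neither makes an exception for withdrawn subjects.

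**The concern.** The population for a primary safety endpoint should be fixed by exposure. Here it also depends on something after exposure, attendance at a later safety visit, and a severe reaction to the infusion can prevent that attendance. Where it does, the subject leaves both the numerator and the denominator because of the event being counted, so the incidence is biased downward.

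The protocol also gives more than one answer to the question of which population carries the safety data of a subject who leaves early. Section 5.22 says the SS. Section 13.3 says the FAS, which such a subject may not belong to either. Section 5.23 requires every event to be tabulated but does not say over which subjects. In a trial of about 15 people, one subject handled one way or the other can change the headline from one severe event to none.

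**Working it through.** **Step 1. Planned denominator.** Sections 5.21 and 7 give three dose groups of 3 with 9-12 subjects in escalation, 6 in expansion, and at least 15 in all. 3 × 3 + 6 = 15 and 12 + 6 = 18. The stated minimum of 15 is reproduced.

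**Step 2. Membership on the literal wording.** Take a subject who received only the first infusion.

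| What happens next | Later safety visit | In the SS (5.22) | In the FAS (5.22) |
| --- | --- | --- | --- |
| Dies before any later visit | Impossible | No | Only if an efficacy evaluation had already been made |
| Lost before any later visit | None | No | Only if an efficacy evaluation had already been made |
| Survives anaphylactic shock, withdrawn under 10.1 | Follow-up required by 8 (item 10), 13.4 and 15.2; not stated whether it counts | Undetermined | Undetermined |

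The flow chart marks adverse events on D1, but 5.22 asks for a visit after dosing and does not say whether same-day observation qualifies.

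**Step 3. Do other sections repair the definition?** Section 5.23 fixes which events are tabulated, not who is in the denominator. Taken with 5.22, it can require an event to be listed for a subject outside the safety population. Sections 13.4 and 15.2 create follow-up but do not mention SS membership, and they cannot help after a death. Section 13.3 points to a set that needs an efficacy evaluation.

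**Step 4. Size if one such subject is excluded.** Exact (Clopper-Pearson) 95% limits, for x events in n subjects:

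- x = 1, lower limit: 1 − 0.975^(1/n). Upper limit: the p that solves (1 − p)^n + n·p·(1 − p)^(n−1) = 0.025.
- x = 0, lower limit: 0. Upper limit: 1 − 0.025^(1/n).

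| Subjects treated | Affected subject kept | Affected subject excluded |
| --- | --- | --- |
| 15 | 1/15 = 6.7% (0.2-31.9%) | 0/14 = 0% (0-23.2%) |
| 18 | 1/18 = 5.6% (0.1-27.3%) | 0/17 = 0% (0-19.5%) |

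For n = 15 the lower limit is 1 − 0.975^(1/15) = 0.0017. For 0/14 the upper limit is 1 − 0.025^(1/14) = 0.232. With 15 subjects, exclusion therefore lowers the estimate by 6.7 percentage points and the upper limit by 31.9 − 23.2 = 8.7 points.

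The direction depends on who is excluded. Dropping an event-free subject instead would turn 1/15 into 1/14 = 7.1%, a small rise. The downward bias arises only when the event itself causes the missing visit.

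**The case against.** The strongest reply is that the protocol plainly intends to keep these patients in view. Subjects withdrawn for an adverse event must be followed, without a time limit in 13.4 and until resolution in 15.2. Everyone infused is to be followed for years under section 8 (item 10). Safety observation begins immediately after the first infusion under 14.1. Section 5.23 demands that all events be tabulated, and any serious event would still be recorded and reported under section 15. The study is also small and mainly descriptive.

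Most of this stands for survivors. A reader might infer that every patient withdrawn for anaphylactic shock drops out of the safety analysis. The documents do not support that: the required follow-up may well count as a safety visit, and nothing says that it does not. What remains is a subject who dies or is lost before any later contact, and the fact that an undefined term decides membership for the others.

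A reader might also infer that escalation decisions are affected, with one toxicity in a cohort of three becoming none in two. The text does not support this either. Sections 5.1 and 9.1 count DLTs among enrolled subjects, the DLT window opens at the start of infusion, and none of these places refers to the SS.

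Finally, the definition might be left to a statistical analysis plan. But the protocol itself fixes the definition, so a plan that dropped the visit condition would contradict it.

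**Conclusion.** The point holds in a limited form. The visit condition in 5.22 serves no purpose and, on its literal wording, excludes a treated subject who dies or is lost after the first infusion. For a survivor withdrawn under 10.1 the outcome is undetermined. Section 5.22 also needs reconciling with 5.23, and 13.3 contradicts it on which set carries adverse reactions.

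The size is 1/15 (6.7%, 0.2-31.9%) against 0/14 (0%, 0-23.2%). This assumes exactly one severe first-infusion event among 15 treated, in a subject who is then excluded under 5.22 despite the instruction in 5.23. No probability is attached, because the protocol gives no rate for such events or for early departure. An assumed departure rate would in any case give the chance of excluding anyone, not of losing a severe event. Severity: should fix, because the primary denominator is involved; the literal gap is narrow and the remedy is wording only.

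**What to change.** 1. In 5.22, define the SS as all subjects who received any amount of UC-MSCs, with no visit condition. A partly given infusion then counts as exposure.
2. State in 5.22 and 5.23 that this set is used for all AE and SAE summaries, so that the events tabulated and the denominator agree.
3. In 13.3, refer to the SS for adverse reactions and keep the FAS for efficacy.
4. Reconcile withdrawal from the trial in 10.1 with the follow-up duties in 8 (item 10), 13.4 and 15.2, so that it is clear which safety data are still collected after withdrawal. The clinical rule itself is for the investigator and sponsor to settle.

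The cost is rewording in a few sections. No visits are added: the flow chart already schedules adverse-event recording from D1 to W28, and longer follow-up is already planned.

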## 14.2 Evaluation Criteria of Efficacy

- Main efficacy criteria:

umbilical cord-derived MSCs infusion can increase the platelet count of the subjects, indicating that the drug is effective.

Evaluation criteria of efficacy:

According to the international consensus of ITP:

- complete response (CR): platelet count ≥ 100 × 10^9^ /L and no bleeding after treatment.
- response (R): platelet count ≥ 30 × 10^9^ /L and at least doubling of the baseline count, and no bleeding after treatment.
- No response (NR): platelet count <30 × 10^9^ / L or less than doubling of the baseline count or bleeding after treatment.
- Relapse: platelet count below 30 × 10^9^/L, or less than doubling of the baseline count, or bleeding, after the achievement of CR or R.

When defining a CR or R, it should be tested at least twice with an interval of at least 7 days.

- Safety efficacy criteria:

The subjects have no obvious adverse reactions caused by umbilical cord-derived MSC infusion, normal vital signs, no hepatitis B, hepatitis C, and other virus infections, and no abnormal organ function. There was no significant difference (P > 0.05) in heart, liver, and renal function between objects before and after treatment, indicating that umbilical cord-derived MSCs have no obvious side effects and are safe.

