# Quality Control and Quality Assurance

## 18.1 Quality Control

1. Determination of study protocol: The clinical study protocol is discussed and negotiated by all investigators participating in this clinical study, and is submitted to the Ethics Committee for approval after reaching a consensus on revision.
2. Control measures of laboratory quality: The manufacturers of umbilical cord MSCs have standardized testing indicators, standard operating procedures, and quality control procedures.
3. Qualification of investigators: Investigators participating in clinical research must have the professional expertise, qualifications and abilities of clinical research, pass the qualification examination. The study needs relatively fixed personnel.
4. Pre-study training: Through pre-study training, investigators can fully understand the clinical study protocol and the specific contents of each index.
5. The criteria for determining abnormalities in laboratory tests are based on the normal reference range of the test unit.
6. All observations and findings in clinical studies should be verified to ensure the data’s reliability and that the conclusions in clinical studies are derived from the original data. Ensure that there are corresponding data management measures in the clinical study and data processing stages.
7. Proactive measures should be taken for possible dropouts to control the shedding rate within 20%.
8. The investigators should ensure that the data are entered into the CRF in a correct (consistent with the actual situation of the subjects), complete (no missing items), clear (neat handwriting and easy to identify), and timely manner according to the original observation records of the subjects.

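### The FAS drops treated subjects with no post-infusion efficacy evaluation from the response-rate denominator, while section 13.3 can be read as keeping them

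*Protocol*

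**What the plan says.** Protocol 5.22 defines the FAS as "All enrolled subjects who received at least one dose of trial medication and had at least one efficacy evaluation", and adds: "The FAS will be used for the efficacy analysis". Section 5.23 sets the estimator: "Proportions with 95% confidence intervals will be calculated for the efficacy endpoint".

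Section 13.3 deals with withdrawn cases, whatever the reason for withdrawal: "the last test results will be considered the final results and will be used for the FAS analysis of their efficacy and adverse reaction". It also provides that subjects who respond before finishing the course "will not be considered as shedding cases but as response ones".

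Section 14.2 requires confirmation: "When defining a CR or R, it should be tested at least twice with an interval of at least 7 days". Its definition of no response rests on the platelet count or on bleeding and does not mention missing data. No section says outright how to classify a treated subject who was never evaluated.

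**The concern.** The FAS condition is met or failed after treatment has started, and the reason for failing it can be the treatment. Section 10.1 withdraws a subject who has a severe allergic reaction during an infusion. If that happens at the first infusion and no later count is taken, the subject has received the product, has not responded, and is absent from the efficacy denominator. There is no control arm in which a similar exclusion could offset this.

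The rules are also uneven. A subject who stops early with a response is kept as a responder under 13.3, while one who stops early without an evaluation is removed by 5.22.

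The two sections also do not fit together. Section 13.3 can be read as putting that same subject back into the FAS with the last available result, which would be the baseline count. Two analysts following the protocol could therefore report different denominators.

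**Working it through.** **Inputs**

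- FAS membership and use: 5.22. Estimator: 5.23.
- Numbers: 9–12 subjects in escalation and 6 in expansion (5.21), at least 15 in total (section 7).
- Counts: weekly in the first month after the first infusion (14.1). The flow chart has a blood routine test at week 1 with a window of ±2 days.
- Baseline: below 30×10⁹/L with bleeding (6.1, criterion 4).
- Responders x and excluded subjects m: **assumed**. The protocol gives neither an expected response rate nor an expected early loss.

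**The plan's own figure.** 9 + 6 = 15 reproduces the stated minimum; the upper end is 12 + 6 = 18. There is no planned response rate to reproduce.

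**Step 1: who is lost**

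| Subject | 5.22 | 13.3 |
|---|---|---|
| Leaves after at least one post-infusion count | In the FAS | In the FAS; last result is final |
| Leaves after infusion 1, before any post-infusion count | Not in the FAS | Can be read as in the FAS with the baseline count, hence no response |

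On the weekly schedule the second row covers only subjects who leave between the first infusion and the week 1 count, at about day 5 to 9 (7 ± 2).

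**Step 2: effect on the rate.** With N treated, x responders and m treated but unevaluated:

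- all treated, unevaluated counted as non-responders: x/N
- FAS under 5.22: x/(N − m)
- difference: x·m / [N(N − m)], which is zero if x = 0 and positive otherwise

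**Step 3: results, with exact (Clopper-Pearson) 95% intervals**

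| N | x | m | All treated | FAS | Shift (points) |
|---|---|---|---|---|---|
| 6 | 3 | 1 | 3/6 = 50.0% (11.8–88.2) | 3/5 = 60.0% (14.7–94.7) | 10.0 |
| 15 | 8 | 1 | 8/15 = 53.3% (26.6–78.7) | 8/14 = 57.1% (28.9–82.3) | 3.8 |
| 18 | 9 | 1 | 9/18 = 50.0% (26.0–74.0) | 9/17 = 52.9% (27.8–77.0) | 2.9 |

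With one exclusion and other assumed responder numbers, the shift at N = 6 runs from 2/30 = 6.7 points (x = 2) to 4/30 = 13.3 points (x = 4). At N = 15 it runs from 4/210 = 1.9 points (x = 4) to 10/210 = 4.8 points (x = 10).

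**Step 4: scale.** The half-width of the interval is (88.2 − 11.8)/2 = 38 points for 3/6 and (78.7 − 26.6)/2 = 26 points for 8/15. The shift is well inside both.

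**Step 5: the wider reading.** The protocol does not define an efficacy evaluation. Section 14.1 also lists efficacy counts by weeks after the four infusions. If only those visits qualified, anyone leaving during the four-week course could be lost. As an outer illustration, suppose shedding reached 20% of 15 = 3 subjects and all of it fell before the first qualifying count. Then 8/15 = 53.3% would become 8/12 = 66.7% (34.9–90.1), a shift of 13.3 points.

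**The case against.** The strongest reply is that the gap is narrow and little depends on it. Most of this stands.

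- A reader might infer that early drop-outs in general leave the denominator. They do not: 13.3 keeps withdrawn cases in the FAS with their last result, and one post-infusion count is enough to qualify. A single count cannot confirm a response under 14.2.
- A reader might infer that bleeding or rescue removes subjects. In 10.1 severe bleeding is a reason to delay dosing, and 11.5 allows emergency treatment without requiring withdrawal. Bleeding after treatment is itself a no-response criterion in 14.2.
- A reader might take the figure in 18.1 ("Proactive measures should be taken for possible dropouts to control the shedding rate within 20" per cent) as the size of the loss. It is a quality target for all shedding over the whole study, most of which 13.3 would keep in the FAS.
- Sections 13.4 and 15.2 require follow-up of subjects who withdraw for adverse events, so a later count may exist. Neither section says that it would serve as an efficacy evaluation.
- Efficacy is a secondary objective and 5.23 calls the analysis mainly descriptive. No hypothesis or success threshold uses the rate. In a trial of about 15, a missing subject would probably be noticed.

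It can also be said that missing responses belong in an SAP, which is not at hand. That does not answer the point, because the protocol is not silent here: 5.22 states an exclusion, and 13.3 states a rule that can contradict it.

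**Conclusion.** The point holds in a narrow form. A treated subject with no post-infusion efficacy evaluation is excluded from the response rate by 5.22 and can be read back in by 13.3. When there is at least one responder, the exclusion can only raise the rate. For one excluded subject the shift is about 7–13 points in a group of 6 (2 to 4 responders) and about 2–5 points in 15 subjects (4 to 10 responders). These sizes rest on assumed responder and exclusion counts, and on weekly counts from the first infusion serving as efficacy evaluations. If only visits after the fourth infusion qualified, the loss could be larger; the text does not settle this.

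No error rate, sample size or decision threshold is affected. The one use beyond description is that 5.1 lists efficacy among the considerations for choosing the expansion dose, without a numerical rule. This is a low-cost correction worth making. It does not show that the efficacy analysis is unsound.

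**What to change.** - In 5.22, define the efficacy set as all subjects who received any UC-MSC infusion.
- In the response proportions, count every subject without a confirmed CR or R under 14.2 as NR, including those never evaluated. For the percentages in 3.2 that need a threshold to be reached only once, use the same denominator and count a never-evaluated subject as not having reached it.
- Align 13.3, so that its last-result rule neither changes the denominator nor turns a single carried-forward count into a confirmed response.
- Keep the present FAS as a sensitivity analysis, and state there which visits count as an efficacy evaluation.

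The cost is a few sentences in two sections. No new data or subjects are needed. The reported response rate may be slightly lower.
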